### Inclusion and exclusion criteria

Inclusion and exclusion criteria for the index trial, target trial and emulated trial are summarised in table 1.

#### Prevalent new-user design

In the PNUD, to be included in the base cohort individuals should have a diagnosis of CF, be aged ≥6 years, have a forced expiratory volume in 1 s (FEV _1_)≥40% predicted at most recent annual review, and prescribed ICS for >3 months before the date of ICS discontinuation, for both the discontinuer in each exposure set and their corresponding continuers. Excluded are those who were prescribed oral corticosteroids and/or intravenous antibiotics in the 1 month prior to the ICS discontinuation date, for both the discontinuer in each exposure set and their corresponding continuers. Exclusion of individuals taking higher doses of ICS as specified in the target trial is not possible in the emulated trial as dosage information is unavailable in the UKCFR.

#### Sequential trials design

The same inclusion and exclusion will be applied in the sequential trials design, except eligibility will be reassessed based on new information (if an annual review encounter takes place) between each successive trial. The criteria are applied at time zero for each trial, where the index date differs between discontinuers and continuers, unlike in the PNUD.

### Variables

Variable specifications are the same in both the PNUD and sequential trials design.

#### Treatment strategies

The treatment strategies for the TTEs differ from the target trial due to lack of a placebo control. Instead, these analyses consider ICS discontinuation based on prescription data as the ‘treatment’ of interest and continued ICS use as the comparator treatment strategy. Whereas the index trial investigates discontinuation of fluticasone propionate only, the target trial and emulated trials are more pragmatic and will include all types of ICS (including in combination with bronchodilators). This reflects the heterogeneity of specific ICS or IC combination treatments documented within the UKCFR.

Discontinuation will be conceptualised as a point treatment strategy (ie, non-time-varying), where treatment status is determined at a single time point (time zero) for both ICS discontinuers and continuers.

These analyses will first estimate the observational analogue of an intention-to-treat (ITT) effect, which is the effect of being assigned to a treatment status.^24^ We will also target a per-protocol (PP) effect, which is the effect of adhering to the assigned treatment strategies. If in the real world individuals deviate from their assigned treatment (ie, discontinuers switch back to being on ICS and vice versa), the ITT and PP estimands differ and the ITT may be less relevant. See *Main analysis* for details.

#### Outcomes

The primary outcome of the TTE is time to first pulmonary exacerbation. There are multiple definitions of exacerbations in CF clinical studies.^25^ In this TTE, we define a pulmonary exacerbation as a course of intravenous antibiotics given either at home or in hospital, as these treatments are reliably recorded in the UKCFR and have been previously used in landmark studies using observational data in CF.^7 26 27^ This differs from the target trial and CF-WISE, where a symptom-based criteria (known as Fuchs’s definition) was used.^12 28^ The analysis will account for the competing events of death and lung transplant.

Secondary outcomes are change in lung function, measured as change in FEV_1_% predicted and forced vital capacity (FVC%) predicted over 6 months. Spirometry values are calculated based on Global Lung Initiative reference equations-2012.^29^ Change is measured as the absolute difference between measures of FEV_1_% and FVC% measured at baseline (measured at the closest annual review preceding time zero) and at the subsequent annual review, provided that occurs at least 3 months following time zero.

Other secondary outcomes specified in the target trial—new/unplanned courses of intravenous antibiotics and rescue bronchodilator usage—will not be assessed due to similarity of UKCFR definitions for intravenous antibiotic courses and the primary outcome (pulmonary exacerbation) in the TTE, and inability to define ‘rescue’ bronchodilator use using the UKCFR data, respectively.

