## Methods and analysis

### Data source

The UK CF Registry (UKCFR) is a centralised national database sponsored and managed by the CF Trust, which collects real-world data from all specialist CF centres in the UK.^15^ It holds data on an estimated 99% of the UK CF population covering demographic and longitudinal clinical data and was highlighted by the UK National Institute for Health and Care Excellence real-world evidence framework as an exemplar data source for evidence generation.^16^

Data collection for the UKCFR began in 1996 and is primarily structured around annual review visits, taking place approximately 1 year apart. In addition, demographic data including sex, ethnicity, diagnosis data and genotype are collected at enrolment into the Registry and usually remain time-invariant. Information is captured annually on events or conditions that have happened since the previous annual review, including complications, infections, treatments and hospital admissions. Other information collected at the date of each annual review includes results from pulmonary function tests, weight and height. Extracts of data recorded at annual reviews are provided to researchers for approved projects. In 2016 variable domains were added, including exact start and stop dates of medications.

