### Study design

We will use UKCFR data to conduct an emulation of a target trial based on the CF-WISE trial. This will be done using two study designs: (1) the PNUD and (2) the sequential trials design.^3 17^ The two study designs use distinct but related approaches to making use of observational data and applying statistical analyses to estimate causal effects, with control for measured confounding and time-related biases being at both design and analysis phases.^3 17^ The data used for these emulations will be from 2016 to 2018, chosen intentionally based on data quality and completeness in the UKCFR data and being in the pre-CFTR modulators era. Table 1 specifies the protocol components of the index trial (CF-WISE), the corresponding target trial (hypothetical RCT we would undertake if it were feasible) and how each element of the target trial will be emulated using UKCFR data.

**Table 1 T1:** Specification and emulation of a target trial of deprescribing from inhaled corticosteroids in the UKCFR

Protocol component	CF-WISE (index randomised trial*)	Target trial	Target trial emulation using UKCFR
Eligibility criteria	People diagnosed with CF aged ≥6 years, with FEV _1_≥40% predicted, sustained ICS use ≥3 months. Recruitment period November 2001 and July 2004. Excluded are people who used oral corticosteroids, high-dose ICS or intravenous antibiotics in the 4 weeks prior to treatment assignment.	Same as CF-WISE, except study period is between January 2016 and June 2018. This period reflects a balance between data quality and completeness in UKCFR and prior to the widespread introduction of CFTR modulators.	Prevalent new-user design*:* Same as target trial, except ICS dosage was not recorded. Individuals are eligible for the base cohort (see *Study design*) on the earliest date within the study period that they meet all eligibility criteria. Sequential trials design: Same as target trial, except ICS dosage not recorded. Successive regularly spaced ‘trials’, with eligibility criteria redefined based on most recent data if available.

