Treatment strategies	Following a 2-month run-in period receiving fluticasone propionate, participants either: continue to take fluticasone, or switch to taking placebo.	Participants either: continue to take ICS (any ICS, not limited to fluticasone propionate) for the duration of follow-up, or discontinue ICS and remain not taking it for the duration of follow-up.	Prevalent new-user design: Same as target trial, with information on (dis)continuation obtained using prescription start and stop dates. Sequential trials design: Same as the PNUD.
Assignment procedures	Randomisation to treatment strategy Investigators and participants blinded to assignment.	Same as CF-WISE.	Prevalent new-user design: For each discontinuer, comparators will be selected into time-based exposure sets that correspond to each ICS discontinuer. Comparators within each exposure set will then be reweighted to resemble the discontinuers. Sequential trials design: Sequence of artificial ‘trials’, with discontinuers and continuers defined within each regularly spaced ‘trial’. Potential for re-use of continuers across multiple trials. Confounder adjustment is through regression. In the absence of randomisation, treatment assignment is assumed to be random conditional on ICS treatment history and the measured covariates specified in *Covariates*.
Follow-up and index date	Follow-up starts at randomisation and ends at loss to follow-up, meeting criteria for early trial withdrawal, or 6 months of follow-up, whichever occurs first.	Same as CF-WISE	Prevalent new-user design: Follow-up starts at date of ICS discontinuation for both the discontinuers and the reweighted continuers. Sequential trials design: Follow-up starts at the date of ICS discontinuation for the discontinuers and the date of the start of each successive ‘trial’ for the continuers in that trial. For the primary outcome, individuals will be followed up to first pulmonary exacerbation, death, transplant or 6 months after treatment assignment, whichever occurs first. For information on follow-up for secondary outcomes (lung function) see online supplemental material appendix 1.

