#### Covariates

In the emulated trials, treatment discontinuation or continuation is not randomised and so measured potential confounders of the relationship between ICS discontinuation and clinical outcomes must be adjusted for to meet the assumption of no unmeasured confounding, a requirement for unbiased causal effect estimation.^30^

Based on a priori clinical expertise, we will adjust for the following covariates at baseline: age, sex, genotype, body mass index z-score, CF-related diabetes, FEV_1_% predicted, home and hospital intravenous antibiotics, hospital admissions, *P. aeruginosa* infection, *Burkholderia* infection, non-tuberculous mycobacteria infection, allergic bronchopulmonary aspergillosis, pancreatic insufficiency, liver disease, inhaled bronchodilator use (captured as a separate variable to ICS), asthmatic status (as a proxy to atopic status specified in CF-WISE), inhaled antibiotic use and mucoactive therapy use (hypertonic saline, mannitol and DNase).

For both the PNUD and sequential trials design, these covariates will be recorded at the nearest annual review date preceding time zero. Since ICS stopping dates may occur at any point between successive annual reviews, stopping dates will occur at various time intervals following baseline annual review across individuals. Therefore, time from previous annual review (in months) to time zero for both the discontinuers and continuers will be adjusted for in the analyses.

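### The secondary lung function outcome is labelled a 6-month change but is defined between two annual reviews about a year apart, starting before time zero

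*Protocol article*

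**What the plan says.** In the Protocol article, Outcomes, the secondary outcomes are change in FEV1% predicted and in "forced vital capacity (FVC%) predicted over 6 months". The same paragraph then gives the working definition. The baseline is "measured at the closest annual review preceding time zero", and the second value is taken "and at the subsequent annual review, provided that occurs at least 3 months following time zero". No upper limit and no 6-month target are set for the second value.

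The Data source section describes the registry as "primarily structured around annual review visits, taking place approximately 1 year apart". The Covariates section states "Since ICS stopping dates may occur at any point between successive annual reviews" as the reason for an added adjustment: "time from previous annual review (in months) to time zero for both the discontinuers and continuers will be adjusted for in the analyses". Baseline FEV1% predicted is also on the covariate list.

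Table 1 gives the secondary outcome as mean change, with no remark on timing, and defers detail: "For information on follow-up for secondary outcomes (lung function) see online supplemental material appendix 1". That appendix is not at hand. The description of CF-WISE gives its follow-up as 6 months.

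**The concern.** The label and the definition describe different quantities. Two reviews about a year apart cannot give a 6-month change. Because the baseline review precedes time zero, part of the measured change belongs to a period before anyone was assigned to stop or continue. That part cannot be an effect of stopping.

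The research aim names lung function alongside exacerbations, and the first objective is consistency with CF-WISE. The article openly flags its other departures on outcomes: the exacerbation definition and the two secondary outcomes it omits. It flags this one neither in Outcomes, nor in Table 1, nor under Limitations. A reader would take the reported figure as the effect 6 months after stopping and compare it with CF-WISE on that footing.

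**Working it through.** The article gives no figure for the split of the interval around time zero or for the share of people with a usable second review, so there is nothing to reproduce. The check derives both.

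**Inputs from the article.** Reviews are about 12 months apart (Data source). Baseline is the last review before time zero, and the second value is the next review if at least 3 months after time zero (Outcomes). Stop dates can fall anywhere between reviews (Covariates). There were 536 discontinuers before the other exclusions (Data checks and feasibility analysis).

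**Assumption.** The distribution of stop dates within the review interval is not given. The base case takes it as uniform.

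**Formulas.** Let L be the months between reviews, U the months from baseline review to time zero, and F = L − U the months from time zero to the second review. With U uniform on 0 to L, and people kept if F ≥ 3:

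- Share not meeting the 3-month condition: 3/L = 3/12 = 25%. For the 536 discontinuers, 0.25 × 536 = 134.
- Mean time before time zero among those kept: (L − 3)/2 = 9/2 = 4.5 months.
- Share of the interval before time zero: (L − 3)/(2L) = 9/24 = 37.5%.
- Mean follow-up after time zero: (L + 3)/2 = 15/2 = 7.5 months, with range 3 to 12.
- Share of those kept who are measured at 5 to 7 months: 2/(L − 3) = 2/9 = 22%.
- Share of those kept who are measured later than 6 months: (L − 6)/(L − 3) = 6/9 = 67%.

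**Sensitivity.**

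| Spacing and stop-date pattern | Fails 3-month condition | Interval before time zero | Mean follow-up (months) |
|---|---|---|---|
| 12 months, uniform | 25% | 37.5% | 7.5 |
| 9 months, uniform | 33% | 33% | 6.0 |
| 15 months, uniform | 20% | 40% | 9.0 |
| 12 months, stops mostly soon after a review, Beta(1,2) | 6% | 30% | 8.4 |
| 12 months, stops mostly before the next review, Beta(2,1) | 44% | 50% | 6.0 |
| 12 months, stops clustered at both ends, Beta(0.5,0.5) | 33% | 29% | 8.5 |
| 12 months, uniform, a too-early review replaced by the following one | 0% | 39% to 40% | 9.0 |

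Letting the spacing vary between people (mean 12 months, SD 1 to 3) leaves the first two results at about 25% and 37.5% to 38%. In the last row the mean interval is 15 months and follow-up runs from 3 to 15 months.

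Two rows have a mean follow-up of 6 months, but the change they measure still spans 9 or 12 months and still starts before time zero. No row gives a 6-month change for everyone.

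**The case against.** The strongest reply is that the plan already handles the timing. Months from the previous review to time zero are adjusted for. With spacing near 12 months, time before and time after time zero add to about 12, so adjusting for one largely adjusts for the other. Both arms take their baseline before time zero. Given the baseline value, an arm contrast in change is the same as an arm contrast in the follow-up value, so the stretch before time zero drops out if the stated exchangeability assumption holds. What remains is unrecorded decline between review and stopping. That is unmeasured confounding, which bears on the primary outcome too and which the article acknowledges. This reply stands as far as it goes, so a reader who took the 37.5% as a measure of bias would be going further than the documents allow. It answers imbalance between arms, however, and not the label. An adjusted contrast averaged over follow-up of 3 to 12 months is still not a contrast at 6 months.

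A second reply is that appendix 1 carries the follow-up and analysis of lung function. It may well model time after time zero. But the main text gives an operative definition that conflicts with its own label, and an appendix does not remove that conflict.

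Third, lung function is secondary. The benchmarking criterion for point estimates is framed around HRs. CF-WISE tested percentage change, whereas the emulation uses absolute change. Numerical comparison was therefore limited already, which lowers the stakes but does not make the label right.

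Three further inferences are tempting but not supported:

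- **A quarter of people are dropped.** Exclusion is the natural reading of the 3-month condition, but the article does not say what happens to an early review. The 25% rests on uniform stop dates, and continuers in the sequential trials design can enter several trials, so the figure fits discontinuers only.
- **Outcome reviews after December 2018 are lost.** The Study design section says "The data used for these emulations will be from 2016 to 2018", but a time zero in January 2016 would generally need a baseline review from before 2016. The phrase therefore cannot be a literal limit on every measurement.
- **The 3-month minimum is an error.** It keeps out people measured days after stopping, and removing it would be a trade-off, not a correction.

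**Conclusion.** The contradiction is real and needs no distributional assumption. The outcome labelled a 6-month change is a change over about 12 months that starts before time zero and ends about 3 to 12 months after it. It cannot be reported as a 6-month effect or compared with CF-WISE as one.

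The figures are illustrations. Under 12-month spacing and uniform stop dates, 37.5% of the interval precedes time zero and 25% of discontinuers would not meet the 3-month condition. With the same spacing and the other stop-date patterns tried, the ranges are 29% to 50% and 6% to 44%. Neither base-case figure is a fact about the registry.

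The point affects what the secondary result can be said to show. The label and timing of the primary outcome are not affected.

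**What to change.** 1. Relabel the outcome as change from the last annual review before time zero to the next annual review.
2. Model the follow-up FEV1% or FVC% value on its baseline value, arm, months from time zero to the outcome review, and the arm-by-months term. Report the arm contrast at 6 months. One time term may suffice, because months to the outcome review is nearly collinear with the time-since-review covariate already planned.
3. State what is done when the next review falls within 3 months of time zero. The minimum itself can stay.
4. Record the timing departure from CF-WISE in Table 1 and under Limitations. If appendix 1 already does some of this, bring the main text into line with it.

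The cost is a change of wording and a modest change to the secondary analysis. The 6-month contrast will rest on a simple model for time and will be less precise than an average over all follow-up times.

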#### Covariates

In the emulated trials, treatment discontinuation or continuation is not randomised and so measured potential confounders of the relationship between ICS discontinuation and clinical outcomes must be adjusted for to meet the assumption of no unmeasured confounding, a requirement for unbiased causal effect estimation.^30^

Based on a priori clinical expertise, we will adjust for the following covariates at baseline: age, sex, genotype, body mass index z-score, CF-related diabetes, FEV_1_% predicted, home and hospital intravenous antibiotics, hospital admissions, *P. aeruginosa* infection, *Burkholderia* infection, non-tuberculous mycobacteria infection, allergic bronchopulmonary aspergillosis, pancreatic insufficiency, liver disease, inhaled bronchodilator use (captured as a separate variable to ICS), asthmatic status (as a proxy to atopic status specified in CF-WISE), inhaled antibiotic use and mucoactive therapy use (hypertonic saline, mannitol and DNase).

For both the PNUD and sequential trials design, these covariates will be recorded at the nearest annual review date preceding time zero. Since ICS stopping dates may occur at any point between successive annual reviews, stopping dates will occur at various time intervals following baseline annual review across individuals. Therefore, time from previous annual review (in months) to time zero for both the discontinuers and continuers will be adjusted for in the analyses.

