## Research aim and objectives

### Research aim

We aim to estimate the causal effects of discontinuing ICS on clinical outcomes (pulmonary exacerbations and lung function) in people with CF using two different study designs in observational data.

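### Change in FVC% predicted is a secondary outcome, but baseline FVC% predicted is missing from the adjustment list, so the FVC change score, unlike the FEV1 one, is not adjusted for its own baseline

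*Protocol article*

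**What the plan says.** The Outcomes section of the protocol article defines the secondary endpoints: "Secondary outcomes are change in lung function, measured as change in FEV_1_% predicted and forced vital capacity (FVC%) predicted over 6 months". It gives their form as follows: "Change is measured as the absolute difference between measures of FEV_1_% and FVC% measured at baseline" (at the annual review before time zero) and at the next annual review.

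The Covariates section introduces its list by saying that "measured potential confounders of the relationship between ICS discontinuation and clinical outcomes must be adjusted for". The Research aim section defines these as "clinical outcomes (pulmonary exacerbations and lung function", so the list is not confined to the primary outcome. The Covariates section then states that "we will adjust for the following covariates at baseline: age, sex, genotype, body mass index z-score, CF-related diabetes, FEV_1_% predicted, home and hospital intravenous antibiotics"; the list goes on through hospital admissions, infections, complications, bronchodilator use and asthma, and ends with "inhaled antibiotic use and mucoactive therapy use (hypertonic saline, mannitol and DNase". FEV1% predicted is in it. FVC% predicted is not.

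The Variables section adds: "Variable specifications are the same in both the PNUD and sequential trials design". Under Main analysis, the same list feeds the propensity-score model of the prevalent new-user design (PNUD), and the sequential design adjusts for the baseline confounders in each trial. Table 1 rests the emulation on assignment being random given ICS treatment history and the listed covariates. The lung-function analysis itself is referred to online supplemental appendix 1, which is not shown.

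**The concern.** A change score does not by itself remove a baseline difference between groups that were not randomised. Part of any single spirometry reading is transient. If people with a high reading are more likely to stop ICS, their next reading tends to fall back whether they stop or not, and the fall is credited to stopping. If people with a low reading stop more often, the sign reverses. Conditioning on the baseline reading removes this. Conditioning on baseline FEV1 removes only the part that FEV1 and FVC share.

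The plan conditions on the outcome's own baseline for FEV1 and not for FVC, and gives no reason for the difference. The FVC estimate is at stake in both designs. Because both would use the same list, agreement between them (Comparison of methods) would not expose a bias that they share.

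**Working it through.** The plan states no SD, correlation, baseline FVC or precision for this outcome, so there is no figure to reproduce. Everything below is conditional on assumed inputs. Effects are discontinuers minus continuers, change is follow-up minus baseline, and the true effect is 0.

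**1. Algebra**

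Assumed inputs:
- SD of FVC% predicted: 18 points.
- Correlation of baseline FEV1 with baseline FVC: 0.85.
- Retest correlation of FVC, r: 0.70, 0.85 or 0.90.
- Correlation of baseline FEV1 with follow-up FVC, q: 0.62, 0.75 or 0.80.
- Difference d in baseline FVC between groups at equal FEV1: 3 points.
- 300 discontinuers and many continuers. The feasibility section gives only 536 discontinuers before the other exclusions.

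Formulas:
- Coefficient of baseline FVC given baseline FEV1: b = (r − 0.85q)/(1 − 0.85²) = (r − 0.85q)/0.2775.
- Bias with FEV1-only adjustment: −(1 − b)d.
- Residual variance of change given FEV1, in SD² units: v = 2(1 − r) − (q − 0.85)².
- Standard error: about 18√v/√300. This ignores the continuers' contribution and any inflation from weighting.

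| r | q | b | Bias, d = 3 | v | SE | Bias/SE |
|---|---|---|---|---|---|---|
| 0.70 | 0.62 | 0.623 | −1.13 | 0.547 | 0.77 | 1.5 |
| 0.85 | 0.75 | 0.766 | −0.70 | 0.290 | 0.56 | 1.3 |
| 0.90 | 0.80 | 0.793 | −0.62 | 0.198 | 0.46 | 1.3 |

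The result scales with d. The SD of FVC given FEV1 is 18√0.2775 = 9.5 points, so d = 3 is 3/9.5 = 0.32 conditional SD. At 0.1 conditional SD (0.95 points) the bias is −0.377 × 0.95 = −0.36, −0.234 × 0.95 = −0.22 and −0.207 × 0.95 = −0.20. That is 0.4 to 0.5 of the same standard errors.

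**2. Simulation: what drives stopping**

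Each reading was a stable level plus visit noise, and stopping followed a logistic model. The SD was 18, the retest correlation 0.80 to 0.90 and the FEV1–FVC correlation 0.70 to 0.85. The correlation between the transient parts of FEV1 and FVC within a visit was 0 to 0.7; the stable-level runs did not vary it. Discontinuers had the higher baseline FVC, by about 3.6 to 6.6 points before adjustment.

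| Stopping depends on | Adjusted for FEV1 only | Adjusted for FEV1 and FVC |
|---|---|---|
| Measured FVC, alone or with FEV1 | −0.14 to −1.1 | within 0.1 of 0 |
| Measured FEV1 only | within 0.1 of 0 | within 0.1 of 0 |
| Stable underlying level | within 0.12 of 0 | about +0.2 to +0.7 |

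In the first row, when the transient parts of FEV1 and FVC correlate 0.7 within a visit, the range narrows to −0.14 to −0.56, because FEV1 then carries more of the same noise. Weighting continuers by PS/(1 − PS), run for one set of scenarios, gave the same pattern as regression.

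**The case against.** **The FVC model is in appendix 1.** The article describes weights and regressions for the time-to-event outcome and sends lung function to a supplement that may include the outcome's own baseline. This stands as a limit: the omission is shown for the article's list only. But the article does not defer the covariate set. It states the set without qualification and for clinical outcomes in general.

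**Imbalance alone is not enough.** A reader might infer that any baseline difference in FVC becomes an apparent effect of stopping. The documents do not support that, and the simulation contradicts it: with stopping driven by FEV1 only, FVC was imbalanced by about 4 to 5 points and the bias after FEV1 adjustment was about 0. Nothing in the article says that stopping depends on measured FVC given FEV1. Eligibility uses FEV1 only, and stop dates can fall anywhere between annual reviews. This objection stands, so the bias is possible but not shown.

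**The size is assumed.** A reader might also infer a bias larger than the standard error. That ratio follows from a 3-point gap at equal FEV1, which would have to persist after all the other listed covariates. No figure in the article supports it. This stands too.

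**The fix can add bias.** If stopping depends on the stable level, the change score is already about right and adjusting for the measured value introduces a few tenths of a point. This is true, but it applies equally to adjusting FEV1 change for baseline FEV1, which the plan already does. It therefore does not justify treating the two outcomes differently.

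**Conclusion.** The point holds as an inconsistency in the adjustment set. The list covers lung function, includes the baseline of one lung-function outcome and leaves out the baseline of the other, although that value is needed to compute the change score. The plan's assumption of random assignment given the listed covariates fails for FVC if stopping depends on measured FVC beyond them.

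Under the assumed inputs the resulting bias lies between near 0 and about −1 point when discontinuers have the higher FVC. The documents do not allow a narrower statement. The case rests on bias and not on precision: at a retest correlation of 0.85, adding baseline FVC lowers the residual variance only from 0.290 to 0.275, about 5%.

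The primary hazard ratio, its benchmarking against CF-WISE and the FEV1 outcome are untouched. This is a modest correction to one secondary outcome, worth making because it costs almost nothing.

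**What to change.** For the FVC outcome only, add baseline FVC% predicted, from the annual review already used for the change score, to the propensity-score model in the PNUD and to the regression model in the sequential design. If appendix 1 already does this, say so in the Covariates section. Report the FVC result with and without the covariate in both designs.

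The cost is one covariate that is already in the data and, in the PNUD, a second set of weights for this outcome. Its strong correlation with FEV1 does no harm, since neither coefficient is interpreted. The one real downside is the few tenths of a point that adjustment may add if stopping follows the stable level. The comparison with and without the covariate would show how far the result depends on that choice.
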